### Study size estimation

The follow-up of at least 30,000 women will generate 90,000 or more women-years within the 5–6 year study period.

The sample size calculation is based on estimates for the incidence of important outcomes in this age group and a market share of 10% for the new HRT product(s) of interest: cardiovascular mortality (0.5%), non-fatal myocardial infarction (0.2%), stroke (0.2%), and VTE (0.3%).

To detect an increased risk of certain outcomes associated with new HRT products with 95% probability and a power of 80%, the roughly required number of women-years of the combined cohort should have the following magnitude for a detectable rate ratio of 3.0: cardiovascular mortality about 44,000 women-years, myocardial infarction 30,000, and venous thromboembolism 20,000. Therefore the expected 90,000 women-years should be sufficient to investigate the adverse events of interest.

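### The planning rate of 0.5% for cardiovascular mortality and its stated requirement of 44,000 women-years cannot both be right, although 90,000 women-years suffices under either

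*Protocol article*

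**What the plan says.** All of the figures stand in the protocol article under *Study size estimation*. The planning incidences are "cardiovascular mortality (0.5%), non-fatal myocardial infarction (0.2%), stroke (0.2%), and VTE (0.3"%). The exposed fraction is "a market share of 10% for the new HRT product(s) of interest". The error rates are set "with 95% probability and a power of 80"%, and the requirements are given "for a detectable rate ratio of 3.0": "cardiovascular mortality about 44,000 women-years, myocardial infarction 30,000, and venous thromboembolism 20,000". No other rate, rate ratio, share or power is given for cardiovascular mortality. The section ends: "Therefore the expected 90,000 women-years should be sufficient to investigate the adverse events of interest".

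**The concern.** With rate ratio, share, significance level and power all fixed, the number of events needed is the same for every outcome. A more frequent outcome reaches that number in fewer women-years. The section has this the wrong way round for cardiovascular mortality: the most frequent outcome on the list is assigned the most follow-up.

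Cardiovascular mortality is the first outcome of particular interest listed under *Confounding and effect-modifying factors*, and cardiovascular effects are the primary aim under *Final analysis*. The stated requirements are the basis for calling 90,000 women-years sufficient. With one of the two numbers wrong, a reader cannot tell how much reserve the study has for this outcome, or how small a rate ratio it could detect.

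**Working it through.** **Inputs from *Study size estimation*.** Rate ratio 3.0; exposed share 0.10; 95% probability, read as a significance level of 0.05; power 80%; rates 0.5% (cardiovascular mortality), 0.2% (non-fatal myocardial infarction) and 0.3% (venous thromboembolism); planned total 90,000 women-years.

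**Assumptions, not stated in the article.** The test is two-sided, the rates are per woman-year, and each stated rate r is the comparator-group rate.

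**Step 1: check without a sample-size formula.** Under common inputs, rate × women-years should be the same for each outcome.

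- Myocardial infarction: 0.002 × 30,000 = 60
- Venous thromboembolism: 0.003 × 20,000 = 60
- Cardiovascular mortality: 0.005 × 44,000 = 220

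Two outcomes agree and the third is 220/60 ≈ 3.7 times as large.

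**Step 2: reproduce the plan's own figures.** The Schoenfeld number of events is

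D = (1.960 + 0.842)² / [0.1 × 0.9 × (ln 3)²] = 7.849 / (0.09 × 1.207) = 72.26.

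The mean event rate in the combined cohort is r × (0.9 + 0.1 × 3) = 1.2r, so women-years = 72.26 / (1.2r) = 60.21 / r.

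| Outcome | r | Computed | Stated |
|---|---|---|---|
| Myocardial infarction | 0.002 | 30,107 | 30,000 |
| Venous thromboembolism | 0.003 | 20,071 | 20,000 |
| Cardiovascular mortality | 0.005 | 12,043 | 44,000 |

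The first two agree within 0.4%. The third does not: 44,000 / 12,043 ≈ 3.7. Rounding D up to 73 events gives 30,417, 20,278 and 12,167, with the same pattern.

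**Step 3: could another method or input explain 44,000?** An unpooled Poisson rate-difference formula gives 30,523, 20,349 and 12,209. Pooled Poisson, two-proportion (with and without continuity correction), Wald log rate ratio, square-root and exact conditional methods were also tried, one- and two-sided, with the stated rate taken as the comparator or the overall rate. At a 10% share, all methods gave between 4,553 and 14,651 for cardiovascular mortality. Shares of 5%, 20% and one third did not reach 44,000 either; the highest result was 27,400, at 5%. Raising power to 99% in the Schoenfeld calculation gives 28,333. At 0.5%, a requirement of 44,000 corresponds to a rate ratio of about 1.8, which the section does not mention.

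**Step 4: work backwards from 44,000.** r = 60.21 / 44,000 = 0.00137, or about 0.14%.

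**Step 5: what 90,000 women-years can detect.** Find the rate ratio R at which the events needed, 7.849 / [0.09 × (ln R)²], equal the events expected, 90,000 × r × (0.9 + 0.1R).

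- r = 0.005: at R = 1.54, about 468 needed and 474 expected, so R is about 1.5.
- r = 0.00137: at R = 2.21, about 139 needed and 138 expected, so R is about 2.2.

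**Step 6: where sufficiency would fail.** For a rate ratio of 3.0, 90,000 women-years is enough down to r = 60.21 / 90,000 = 0.00067, or about 0.07%.

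**The case against.** The strongest reply is that nothing turns on the error. The planned 90,000 women-years exceeds both 12,000 and 44,000, so the section's conclusion holds whichever number is corrected. If 0.5% is right, 44,000 merely errs on the safe side. The study is non-interventional, and the article ties no stopping rule or test to this figure. All of that stands, and it limits the severity.

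The reply that the requirements are offered only as rough magnitudes does not stand. The two neighbouring figures fit within 0.4%, and roughness does not cover a 3.7-fold gap or a reversed order.

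A reader might infer that the study is underpowered for cardiovascular mortality, for instance by supposing that 0.5% is a decimal slip for 0.05%. At that rate the same formula gives 60.21 / 0.0005 ≈ 120,400 women-years, above the planned total. The document does not support this: 0.05% is neither the stated rate nor the one implied by 44,000. The scenario also depends on the 10% share. *Study participants* describes selecting one woman from each of the two comparison groups for each new-product user, a share of about one third. At that share, D = 7.849 / [(1/3)(2/3) × 1.207] ≈ 29.3, and even 0.05% would need only 29.3 / (0.0005 × 1.667) ≈ 35,100.

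A reader might also infer that 0.5% must be the wrong number because it exceeds the non-fatal infarction and stroke rates combined (0.4%). That is no contradiction. Cardiovascular mortality is a different endpoint that takes in other cardiovascular deaths, and judging the rate too high would need outside data.

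**Conclusion.** The section is internally inconsistent: at the stated inputs, 0.5% and 44,000 women-years cannot both be right. Either the requirement at 0.5% is about 12,000, or the rate behind 44,000 is about 0.14%. The document does not show which. The constant-product check needs only common inputs across outcomes; the figures of 12,000 and 0.14% also rest on the assumptions of a two-sided test and comparator rates per woman-year.

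The sufficiency conclusion for a rate ratio of 3.0 is not overturned. What remains unclear is the margin: 90,000 is about 7.5 times the requirement in one case (90,000 / 12,043) and about twice in the other (90,000 / 44,000). This bears on interpretation, because *Final analysis* treats relative risks under 2.0 to 3.0 as inconclusive. A detectable rate ratio of 1.5 lies below that band and one of 2.2 lies inside it. The point is a should-fix correction of a stated planning figure.

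**What to change.** Trace the source of the cardiovascular-mortality rate and of the 44,000. Then restate rate and requirement as a consistent pair: 0.5% with about 12,000 women-years, or 44,000 with the rate actually used to derive it. The value of about 0.14% is only a back-calculation and should not be entered as the intended rate unless the source confirms it. In the same paragraph, restate the margin for this outcome at 90,000 women-years (detectable rate ratio about 1.5 at 0.5%, about 2.2 at 0.14%), and say that the test is two-sided and the rates are per woman-year in the comparator group, if that is so. The cost is one corrected paragraph; recruitment, follow-up and analysis are unaffected.

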### Evaluation

Based on *a priori *considerations of the clinical pharmacology of the new continuous-combined HRT Angeliq^® ^and also other HRTs, there is a substantial potential for confounding in this study. It will not be possible to confine the study to non-predisposed women, since an important objective in this study is to determine risk according to the baseline risk status. It will be important to control confounding and to evaluate possible effect modification from various sources. Reported serious adverse events will be validated with medical records. Ascertainment of deaths - in particular sudden death - will be accomplished by cross-reference to relevant death registries (in countries were access to these registries are permitted by national law).

### Interim evaluations

Descriptive statistics of the interim results will be presented twice a year to the Advisory Council, including data on the number of women enrolled in the three user cohorts, observed duration and type of HRT use, number and nature of serious AEs for all three HRT cohorts, and as soon as sufficient numbers are available also stratified by starters and switchers, or - if relevant - by certain formulations or specific events (e.g. sudden death, cardiovascular events, or other major events), provided that sufficient numbers have been obtained or the nature of the events is serious, unexpected, or relevant for the study objectives.

Any adverse events mentioned in the follow-up questionnaires or received as separate reports will be compiled by local investigators and forwarded to the international coordinating center in Berlin. Additional information will be sought as appropriate: Firstly, the reporting patient will be contacted again to confirm the absence of misunderstanding and to acquire more information about symptoms and other circumstances. These include confirmation of name/address of the treating physician. Depending on the results, contact will be made with relevant health professionals to gain access to detailed medical information to confirm the (new) event/diagnosis. The clinical seriousness, causality, and possible association of each reported adverse event with HRT use will be assessed.

For the overall safety assessment, the relevant data as well as conclusions will be submitted to the Advisory Council as part of the next scheduled progress report, or immediately in case of urgency. There may be a need for interim safety reports that can be published after assessment by the AC.

### Final analysis

The primary aim of the analysis is to assess cardiovascular effects; the secondary objective is to evaluate all other outcomes of the long-term observation. A detailed analysis plan was prepared and reviewed/approved by the Advisory Committee in September 2004 and March 2005.

Several issues have to be considered in the analysis and interpretation. For example, it cannot be excluded that women who were prescribed the most recently launched HRT (here Angeliq^®^) will be found systematically to be at higher risk than women who were prescribed older HRTs. In addition, it cannot be excluded that starters (first ever users) of the *new *continuous-combined HRT (Angeliq^®^) have an even higher baseline risk than starters of other recent HRTs due to the physicians' prescription behavior, which is influenced by the expectation of a safer "*new HRT*". Furthermore, women who have previously used older HRTs may be at lower risk than new users, because, on average, these will have used the older HRTs for a longer period of time whereas those who experienced cardiovascular events will no longer be using them. Comparisons between first-time users of HRTs should therefore be easier to interpret.

To adjust for confounding and effect modification, multivariate methods will be used. It is anticipated that there may be complex sources of bias and confounding, e.g. many risk factors could contribute to the relevant outcomes. In interpreting the findings, therefore, the greatest emphasis will be on relative risk estimates of high magnitude. Low relative risk estimates (under 2.0 - 3.0) will be considered inconclusive, because it is methodologically impossible to distinguish between causation, bias, and confounding. Any apparently increased relative risk, if present, will be evaluated based on the magnitude of the observed hazard ratio. In interpreting the impact of results on public health (safety), the main emphasis will be on absolute risk estimates.

The focus will be on prudent analysis with appropriate statistical adjustment procedures across centers and countries. Comparisons among countries are not the aim of the study but could be made on request of the Advisory Council.

The final analysis will be based on life-table methods comparing the three main cohorts of users. All analyses will make allowance for confounding, using methods that will include multivariate techniques such as Cox regression, stratification by the Mantel-Haenszel procedure, and exclusion of women with specific confounders at baseline. Some confounders that can be precisely quantified (e.g. smoking status, obesity) will not be excluded but rather controlled for in the analysis.

### Ethics and privacy

The planning and performance of the study are subject to national laws. The study was only started after meeting all requirements of the appropriate regulatory authorities. It will be conducted in accordance with the ethical principles of the Declaration of Helsinki. The study was approved by the ethical committee in Duivendrecht, The Netherlands (Medisch Ethische Toetsingscommissie of the Stichting Therapeutische Evaluatie Geneesmiddelen) in May 2004. The study is registered in the public clinical trials registry of the US National Library of Medicine under the registration number NCT00214903.

The women participate on a voluntary basis. The women will be asked if they are willing to participate, i.e. to report complaints/symptoms/events for years under the assumption that their data will be kept anonymous and will be evaluated/reported as statistics only. The nature of the study will be explained to each woman prior to her entry into the study, including its purpose and associated procedures as well as the expected duration of the study, i.e. including potential benefits and side effects of HRT. After consenting, the women will receive signed and dated duplicates of the volunteer information and informed consent forms. Each woman will have ample opportunity to ask questions and will be informed about the right to withdraw from the study at any time without any disadvantage and without having to provide reasons for this decision.

Women and treating physicians will be kept anonymous in the scientific database. Names and addresses will be stored under lock and separately from the scientific (questionnaire) data. Protocol and study material were submitted to the relevant Data Privacy Institution. The specifications of the respective data protection laws will be followed.

### Advisory council

An independent Advisory Council (AC) consisting of epidemiologists, gynecologists, cardiologists, and other experts of international reputation is responsible for overseeing the study. The AC met for the first time on 18 February 2004. Names and terms of reference are given in the annex. The AC will continue to meet several times during the study period. Non-voting representatives of the sponsor and the investigator will attend the meetings. At the end of each meeting the AC evaluates the findings in executive sessions without the investigator and the sponsor.

### Study management

The Centre for Epidemiology & Health Research Berlin, an independent scientific institution experienced in international, multicentric observational studies, is responsible for planning and conducting the study in Europe. It will coordinate the fieldwork in different countries and subcontract with local investigators to handle language barriers.

## Discussion

Estrogen/Progestagen combinations increase the risk of venous thromboembolism, as a class. As illustrated by the WHI study on HRT these products increase venous thromboembolism maximally during the first year of use, after which the risk declines (starter effect) [1]. Women who are susceptible to VTE probably experience a thrombosis soon after they start HRT intake and then stop treatment. Therefore, a population of long-term users who do not switch between different preparations includes only a few high-risk patients and therefore has a low VTE rate. The starter effect repeats itself at a lower level after a period of discontinuation (re-starter effect) [7,8]. Furthermore, women at high risk tend selectively to switch to the most recently marketed product (switcher effect). For the sake of the validity of the study results and the comparability of the cohorts it is essential to record precise information on duration of use, discontinuation periods and risk factors. Long-term users of a HRT preparation should not be included in the study.

The diagnosis of venous and arterial thromboembolism is not always confirmed by methods with a high sensitivity and specificity (e.g., phlebography). Therefore, the classification of reported thromboembolic events has to be done by a predefined algorithm. Definite and probable events will be considered as confirmed. All other cases will be classified as "not confirmed".

One of the most crucial factors to ensure the validity of the study is a low "lost to follow-up" rate. In order to minimize loss to follow-up a multi-faceted, four level follow-up process was established. The level1 activities include the mailing of the follow-up questionnaire and - in case a woman does not respond - two reminder letters. If level1 activities do not lead to a response multiple attempts are made to contact her, her husband, friends, relatives and the gynecologist/primary care physician per phone. In parallel to these level2 activities searches in national and international telephone and address directories are started (level3 activities). If this is not successful, an official address search via the respective governmental administration is conducted (in some countries centralized, in others decentralized at community level). This level4 activity can provide information on a new address (or information that the respondent has moved abroad or has died). If necessary, a search in the national death registers could be started at the end of the study to clarify the vital status of patients who are lost to follow-up after level4 activities. Overall, the investigators estimate that the loss to follow-up of the combined cohort could be kept at less than 5% of the recruited population.
